## Abstract

**Introduction:**

Inguinal hernia repair is one of the most common surgical procedures performed worldwide. Minimally invasive approaches (laparoscopic and robotic) are increasingly recommended owing to their favorable postoperative outcomes. However, their use in inguinoscrotal hernias remains limited. This study aims to evaluate and compare clinical outcomes of minimally invasive and open approaches in inguinoscrotal hernia repair.

**Methods and analysis:**

This national multicenter prospective observational cohort study will include patients undergoing elective or urgent repair of European Hernia Society-classified inguinoscrotal hernias (S1–S3) using open, laparoscopic, or robotic techniques. Adults (>18 years) from various hospitals in Madrid will be recruited. Data on patient demographics, intraoperative variables, postoperative complications, postoperative pain (Visual Analog Scale score), quality of life, and hernia recurrence over a 2-year follow-up will be collected. A minimum of 100 patients (50 per group) is required for detecting statistically significant differences, assuming 5% loss to follow-up.

**Ethics and dissemination:**

The HM Hospitales Ethics Committee has approved the study protocol. Written informed consent will be obtained from all participants. Results will be submitted to peer-reviewed journals and presented at national surgical conferences.

## Introduction

Inguinal hernia repair is among the most frequently performed surgeries globally, accounting for more than 20 million procedures performed annually [1]. Although most of inguinal hernias are straightforward to repair, inguinoscrotal hernias represent a particularly complex subset, characterized by the descent of the hernia sac into the scrotum. These hernias are associated with larger defect sizes, a more difficult dissection, increased operative times, and a higher risk of complications, including orchitis, testicular atrophy, and wound-related issues [2, 3]. In high-income countries, their incidence is relatively low, accounting for approximately 5%–6% of all groin hernias [4]. However, the rate of inguinoscrotal hernias is substantially higher in low- and middle-income regions owing to delayed diagnosis and limited access to elective hernia repair [5]. Therefore, they pose a considerable burden for both patients and healthcare systems, particularly in terms of morbidity and quality of life (QoL).

The introduction of minimally invasive approaches, including laparoscopic transabdominal preperitoneal (TAPP) and totally extraperitoneal (TEP) repair, has significantly advanced inguinal hernia surgery. Several randomized controlled trials and meta-analyses have indicated that minimally invasive surgery is associated with reduced postoperative pain, fewer wound complications, earlier return to work, and better cosmetic outcomes than open anterior repair [6–8]. Robotic-assisted hernia repair has emerged more recently and appears to provide comparable safety and feasibility, with potential advantages in terms of dexterity, ergonomics, and visualization [9].

Despite these developments, evidence specifically addressing inguinoscrotal hernias remains scarce. Most clinical trials have excluded or underrepresented patients with large inguinoscrotal defects, leaving a knowledge gap regarding the optimal surgical approach for this subgroup [10]. The European Hernia Society (EHS) guidelines acknowledge the potential advantages of minimally invasive approaches but highlight that their use in complex hernias, including inguinoscrotal types, should be limited to surgeons with sufficient expertise and in centers with adequate resources [11]. Currently, only small retrospective series or single-center studies have evaluated laparoscopic or robotic repair in inguinoscrotal cases, frequently underscoring longer operative times and higher technical demands, but with promising results regarding recovery and complication rates [12, 13].

The SCAR study aims to compare short- and long-term clinical outcomes of open versus minimally invasive (laparoscopic and robotic) approaches for inguinoscrotal hernia repair. Particularly, this study will evaluate perioperative complications, postoperative pain, hospital stay, QoL, and long-term outcomes (e.g., recurrence and chronic pain).

## Main and Secondary Hypothesis

We hypothesize that minimally invasive approaches—both laparoscopic and robotic—will lead to better early postoperative outcomes compared with open repair in patients with inguinoscrotal hernias. Specifically, we expect lower rates of surgical site infections and overall complications (as graded by the Clavien–Dindo classification), reduced postoperative pain as measured by the Visual Analogue Scale, and shorter hospital stays.

We also hypothesize that these advantages will translate into an improved early health-related quality of life, as assessed through the EQ-5D-5L questionnaire.

Regarding long-term results, we hypothesize that minimally invasive repair may be associated with lower rates of chronic pain and better long-term quality of life compared with open surgery.

Additionally, we expect that recurrence rates at 2 years will not significantly differ between minimally invasive and open approaches, reflecting comparable long-term durability of the repair.

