### Sample Size Calculation and Justification

The sample size was calculated to detect clinically significant differences in postoperative outcomes between minimally invasive (laparoscopic or robotic) and open approaches for inguinoscrotal hernias. Specifically, the calculation was based on the hypothesis that minimally invasive approaches would decrease postoperative complication rates by 20% compared with open surgery and lead to a 2-point reduction in postoperative pain (measured using the Visual Analog Scale).

Assuming a 5% significance level (two-sided α) and 80% power (1−β), and accounting for an estimated 5% loss to follow-up, a total of 150 patients (50 per surgical group: open, laparoscopic, robotic) will be required. This sample will enable the detection of statistically and clinically meaningful differences across the three groups using analysis of vairance (ANOVA) or Chi-square tests as appropriate.

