### Statistical Analyses

Statistical analysis will follow the intention-to-treat principle. Descriptive statistics will be employed for summarizing baseline characteristics and perioperative outcomes across the three surgical groups: open, laparoscopic, and robotic.

Univariate analyses (Chi-square or Fisher’s exact test and ANOVA or Kruskal–Wallis test for categorical and continuous variables, respectively) will be performed for comparing outcomes, including complication rates, recurrence, surgical site infections, and hospital length of stay.

To control for potential confounders, multivariate logistic regression models will be applied, particularly for primary outcomes, including postoperative complications (classified using the Clavien–Dindo classification system and Comprehensive Complication Index), hernia recurrence, and chronic postoperative pain.

Time-to-event outcomes (e.g., time to recurrence) will be analyzed using Kaplan–Meier survival curves and compared using log-rank tests. To assess predictors of recurrence or reoperations, Cox proportional hazards models will be employed.

Subgroup analyses will be considered on the basis of patient age, BMI, hernia type (primary vs. recurrent), and surgical approach. P < 0.05 will be considered statistically significant.

To assess data quality, protocol adherence, and recruitment balance across centers, an interim descriptive analysis may be performed following the inclusion of 50% of the expected patient sample.

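### A non-significant 2-year recurrence difference would not show comparable durability: no margin or interval criterion is stated, and a true doubling would usually be missed

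*Protocol article*

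**What the plan says.** In the protocol article, Main and Secondary Hypothesis states the expectation that "recurrence rates at 2 years will not significantly differ between minimally invasive and open approaches, reflecting comparable long-term durability of the repair".

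Statistical Analyses gives recurrence several analyses:
- univariate tests across the three surgical groups;
- adjusted models ("To control for potential confounders, multivariate logistic regression models will be applied");
- Kaplan–Meier curves with log-rank tests;
- Cox regression ("To assess predictors of recurrence or reoperations, Cox proportional hazards models will be employed").

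All of these look for a difference or for predictors, judged at the 5% level. No equivalence or non-inferiority margin is stated, and no confidence-interval criterion.

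Sample Size Calculation and Justification rests on a fall in complication rates and a 2-point fall in pain score. It concludes that "a total of 150 patients (50 per surgical group: open, laparoscopic, robotic) will be required", after "accounting for an estimated 5% loss to follow-up". Recurrence plays no part in it, and no expected recurrence rate appears anywhere in the article.

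Outcome Measures lists recurrence as secondary. Statistical Analyses names it among the primary outcomes for the adjusted models.

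**The concern.** A test that fails to reject no difference does not show that two procedures are alike. It may only show that there were too few events to tell them apart. A hypothesis met by non-significance is met more easily the less power the study has, so it puts no real demand on the data.

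This matters because a separate 2-year publication is planned, and the Discussion says the study should inform future guideline recommendations. A statement that minimally invasive repair is as durable as open repair could then rest on data that are also compatible with a large excess of recurrences.

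**Working it through.** **Plan's own figure.** There is none for recurrence: no rate, event count, power or margin. The 150 cannot be reproduced with certainty either, because no baseline complication rate or pain SD is given. One unstated choice comes close. For a fall from 25% to 5%, n = [1.96·√(2·0.15·0.85) + 0.84·√(0.25·0.75 + 0.05·0.95)]² / 0.20² ≈ 49 per group, and 49/0.95 ≈ 52. That calculation says nothing about recurrence.

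**Inputs**
- From the article: 50 per group in three groups, so 50 open and 100 minimally invasive (MIS); 5% loss; two-sided 5% level.
- Evaluable: 50 × 0.95 = 47.5 and 100 × 0.95 = 95, taken as 47 and 95, total 142.
- Assumed, because the article gives none: open 2-year recurrence of 2% to 10%.

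**Step 1: expected events if the rates are equal** (142 × p)
- 2%: 2.8; 3%: 4.3; 5%: 7.1; 8%: 11.4; 10%: 14.2.
- If MIS doubles a 5% open rate, the expected count is 47 × 0.05 + 95 × 0.10 = 11.9.

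**Step 2: chance of a non-significant result if MIS truly doubles recurrence.** The Fisher and Pearson chi-square columns come from exact enumeration: the binomial probabilities of every table with p < 0.05 are summed and subtracted from 1. The log-rank column is the Schoenfeld approximation, power = Φ(√(d·a(1−a))·ln 2 − 1.96), with d the events expected under the doubling and a = 95/142. It is rough with so few events.

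| Open vs MIS | Fisher | Chi-square | Log-rank (approx.) |
|---|---|---|---|
| 2% vs 4% | 99% | 98% | 89% |
| 3% vs 6% | 97% | 94% | 86% |
| 5% vs 10% | 90% | 86% | 80% |
| 8% vs 16% | 80% | 75% | 71% |
| 10% vs 20% | 72% | 68% | 65% |

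The three-group chi-square, simulated with both MIS groups doubled, has power of about 12% at an open rate of 5% and 25% at 10%. It is therefore non-significant about 88% and 75% of the time. Power against a doubling in the two-group comparison reaches roughly 50% only when open recurrence is about 15%.

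**Step 3: width of the interval.** Half-width = 1.96·√[p(1−p)(1/47 + 1/95)].
- 5%: 1.96·√(0.0475 × 0.0318) = 0.076, or 7.6 points.
- 2%: 4.9 points. 10%: 10.5 points.

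With 5% observed in both groups, the crude data would thus be compatible with an MIS rate up to about 7.6 points higher than open.

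**Step 4: sensitivity to the sample size.** The Abstract gives a different total: "A minimum of 100 patients (50 per group) is required for detecting statistically significant differences, assuming 5% loss to follow-up". With 47 evaluable per group, 5% vs 10% is non-significant 94% of the time by Fisher, 83% by chi-square and 85% by the log-rank approximation. The conclusion does not depend on which total is right.

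**Step 5: scale of a real durability claim (illustration only).** Assume equal 5% rates, a 5-point margin, one-sided 2.5% level and 80% power at 1:2. Open n = (1.96 + 0.84)² × 0.05 × 0.95 × (1 + 1/2) / 0.05² ≈ 224, with 448 MIS, 672 in all. At 1:1 the total is 598. About 142 evaluable are planned.

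**The case against.** The sentence is a prediction in a hypothesis section. Recurrence is listed as secondary, and no power is claimed for it. A reader might infer that the plan formally declares comparability whenever p is 0.05 or more. The document does not say that: Statistical Analyses contains no such rule and claims no equivalence test. That much of the objection stands. It does not remove the point, because the hypothesis itself says what non-significance would reflect and nothing else in the article offers another basis for a durability conclusion.

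A reader might also take about 7 events as a property of the study. It is not: it needs an assumed 5% in both groups and 142 evaluable, and it does not apply to a doubling from 5%, where about 12 are expected.

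Nor does listing several recurrence analyses amount to a contradiction. The article gives them different roles (unadjusted comparison, confounder control, time to event, predictors), and the choice of a deciding analysis is detail an article may leave to the analysis plan.

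Finally, it is tempting to answer sparse events by dropping the multivariable models for one crude Kaplan–Meier difference. This is a non-randomized cohort in which each center follows its own routine and surgeon expertise, so that would remove the confounding control and let a durability claim rest on a crude contrast.

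**Conclusion.** The point holds as an invalid inference written into the hypothesis: non-significance is tied to comparable durability, with no margin or interval criterion and in a study not sized for recurrence. For assumed open rates of 2% to 10% and 47 vs 95 evaluable, a true doubling would go unflagged 72% to 99% of the time by Fisher and 68% to 98% by chi-square, with about 65% to 89% by the rougher log-rank approximation.

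The direction is robust across tests, rates in that range and both stated sample sizes; the exact percentages are not, since the rates are assumptions. The interval widths are crude, and adjustment would usually widen them. The change should be made before the 2-year data are seen, but it concerns a long-term outcome and does not call the early outcomes into question.

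**What to change.** - **Main and Secondary Hypothesis:** remove the step from non-significance to comparable durability, and state the recurrence aim as estimation.
- **Statistical Analyses:** report the 24-month recurrence difference, pooled MIS minus open, with a two-sided 95% confidence interval, both crude and confounder-adjusted. Keep the adjustment, using a method suited to few events that gives a risk difference, for example propensity-score weighting.
- **Conclusion rule:** use the word comparable only if the upper limit of the adjusted interval lies below a margin that is clinically justified and fixed before data are seen. Otherwise describe the result as inconclusive or descriptive.

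The cost is wording in two sections and agreement on a margin; no added patients or visits. The downside is that the likely 2-year conclusion becomes inconclusive rather than comparable.

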## Methods and Design

The SCAR study is a prospective multicenter non-randomized observational cohort study conducted across eight centers in Madrid (Spain) specializing in abdominal wall surgery. The objective is to compare clinical outcomes of inguinoscrotal hernia repairs performed via minimally invasive approaches (laparoscopic or robotic) versus open surgery.

Local approval was necessary for the individual participating centers. Patients eligible to participate in the study will be approached by the investigators and subsequently recorded. All included patients will sign a written informed consent form before study initiation.

### Study Population and Eligibility Criteria

All consecutive patients undergoing surgical repair for inguinoscrotal hernia will be considered eligible when they meet all of the following criteria at the time of enrolment:

### Inclusion Criteria

• Age ≥18 years;• Diagnosis of inguinoscrotal hernia classified as either S1, S2, or S3 according to the EHS guidelines [11];• Indication for surgical repair performed either electively or in an urgent setting; and• Surgical approach using either open, laparoscopic, or robotic technique according to the standard practice of each center.

### Exclusion Criteria

• American Society of Anesthesiologists (ASA) physical status >3;• Inability to sign the informed consent and age <18 years; and• Refusal to participate or provide signed informed consent.

### Sample Size Calculation and Justification

The sample size was calculated to detect clinically significant differences in postoperative outcomes between minimally invasive (laparoscopic or robotic) and open approaches for inguinoscrotal hernias. Specifically, the calculation was based on the hypothesis that minimally invasive approaches would decrease postoperative complication rates by 20% compared with open surgery and lead to a 2-point reduction in postoperative pain (measured using the Visual Analog Scale).

Assuming a 5% significance level (two-sided α) and 80% power (1−β), and accounting for an estimated 5% loss to follow-up, a total of 150 patients (50 per surgical group: open, laparoscopic, robotic) will be required. This sample will enable the detection of statistically and clinically meaningful differences across the three groups using analysis of vairance (ANOVA) or Chi-square tests as appropriate.

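### The abstract asks for 100 patients in two groups and the sample-size section for 150 in three, and the three-group tests used to justify the 150 do not test minimally invasive versus open repair

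*Protocol article*

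**What the plan says.** **Size.** The abstract (Methods and analysis) states: "A minimum of 100 patients (50 per group) is required for detecting statistically significant differences, assuming 5% loss to follow-up". Fifty per group with 100 in total means two groups. The section Sample Size Calculation and Justification states instead that "a total of 150 patients (50 per surgical group: open, laparoscopic, robotic) will be required", at a "5% significance level (two-sided α) and 80% power" and "accounting for an estimated 5% loss to follow-up". The abstract gives the 5% loss but no significance level or power.

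**Question.** Main and Secondary Hypothesis expects that minimally invasive approaches, both laparoscopic and robotic, "will lead to better early postoperative outcomes compared with open repair in patients with inguinoscrotal hernias". Methods and Design says: "The objective is to compare clinical outcomes of inguinoscrotal hernia repairs performed via minimally invasive approaches (laparoscopic or robotic) versus open surgery". The first paragraph of the sample-size section uses the same contrast: it assumes that "minimally invasive approaches would decrease postoperative complication rates by 20% compared with open surgery", and a 2-point lower score on the Visual Analog Scale (VAS).

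**Test.** The second paragraph of that section says the sample allows "detection of statistically and clinically meaningful differences across the three groups" with ANOVA or Chi-square. Statistical Analyses summarises three groups and lists Chi-square or Fisher and ANOVA or Kruskal–Wallis as univariate tests. It then plans multivariable logistic models for confounding, chiefly for the primary outcomes, and does not say how surgical approach enters them.

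**The concern.** A study should have one recruitment target and a sample size tied to the comparison it sets out to make. Here the total differs by 50 patients between two current statements. That also moves the optional interim look at half the expected sample: 50 patients on one figure, 75 on the other.

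The second problem is one of inference. A three-group test asks whether any of the three groups differs from the others. A gap between laparoscopic and robotic repair alone can make it significant, and such a result could be reported as support for a hypothesis about minimally invasive versus open repair. In the other direction, a real effect shared by both minimally invasive techniques is spread over 2 degrees of freedom (df), so the test is less sensitive to it than a single contrast on the same patients.

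**Working it through.** **Step 1. Can either total be reproduced?** No. The plan gives alpha 0.05 two-sided, 80% power, 5% loss, a 20% decrease and 2 VAS points. It gives no open-group complication rate and no VAS standard deviation (SD), and it does not say whether 20% is absolute or relative. Under assumed inputs, 50 per group matches an ordinary two-group calculation:

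- 24% versus 4% needs 47 per group, and 47 / 0.95 = 49.5, so 50.
- 2 VAS points with SD 3.45 needs 47 per group, so again 50 after loss.
- 30% versus 10% needs 62, and 62 / 0.95 = 65.3, so 66.

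So 100 fits a two-group design, and 150 looks like the same group size used three times. That is an inference; the plan does not say it.

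**Step 2. Does the three-group test answer the stated question?** Evaluable per group: 50 × 0.95 = 47.5. Assume open 30%, laparoscopic 20%, robotic 40%. With equal numbers, minimally invasive as a whole is (20 + 40) / 2 = 30%, the same as open.

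- Noncentrality λ = n Σ(pᵢ − p̄)² / [p̄(1 − p̄)], with p̄ = 0.30.
- λ = 47.5 × (0 + 0.01 + 0.01) / 0.21 = 4.52.
- The 2-df Chi-square at 5% then rejects with probability 0.46.

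**Step 3. Power for the stated effect.** Assume equal laparoscopic and robotic rates and exact 1:1:1 enrolment. The pooled test compares 47.5 open with 95 minimally invasive patients: power = Φ[(d − 1.96 × SE₀) / SE₁], where SE₀ uses the common rate and SE₁ the separate rates.

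Example, 30% versus 10%:

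- Three groups: p̄ = 0.50 / 3 = 0.1667; λ = 47.5 × (0.1333² + 2 × 0.0667²) / (0.1667 × 0.8333) = 9.12; power 0.776.
- Pooled: SE₀ = 0.0662, SE₁ = 0.0733; (0.20 − 1.96 × 0.0662) / 0.0733 = 0.958; power 0.831.

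| Assumed open vs minimally invasive | Three-group, 2 df (150) | Pooled contrast, 1 df (150) | Two groups of 47.5 (100) |
|---|---|---|---|
| 25% vs 5% | 89% | 91% | 79% |
| 30% vs 10% | 78% | 83% | 69% |
| 40% vs 20% | 62% | 71% | 57% |
| 50% vs 30% | 54% | 65% | 51% |
| 30% vs 24% (relative 20%) | 10% | 12% | 10% |

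The last column is the power of the abstract's version, and also of any single unadjusted pairwise comparison within the 150.

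**Step 4. Patients needed for the pooled contrast.** At one open to two minimally invasive patients, 80% power and 5% loss, the totals are 108 (25% vs 5%), 139 (30% vs 10%), 190 (40% vs 20%) and 218 (50% vs 30%). Whether 150 is enough therefore depends on a rate the plan does not state.

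**The case against.** The strongest reply has four parts.

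- **The abstract is simply out of date.** It says minimum, the sample-size section is the operative text, and that section agrees with Statistical Analyses on three groups. This is the likelier reading. A reader might infer two live targets, so that stopping at 100 would comply with the plan; the documents do not support going that far. The two figures still disagree and the abstract still needs correcting.
- **The adjusted models may do the real work.** In a non-randomized cohort the logistic models are the natural inferential analysis, and they could carry a minimally invasive versus open term. That is fair, and such coding, like any pairwise follow-up, is commonly left to an analysis plan that is not shown. So one cannot say that no such contrast is planned, or that pairwise comparisons would be post hoc. What remains is that the sample size is justified by the three-group tests and not by those models.
- **Three groups are part of the purpose.** The hypothesis names both laparoscopic and robotic repair, which can mean each against open, and the Discussion promises data on all three techniques. Describing three groups is therefore legitimate, and pooling is one reading of the contrast. On the other reading the three-group test still tests neither comparison with open.
- **Power may be adequate.** At 25% versus 5% both tests exceed 80% and differ by about 2 points. If the 20% is relative, power is so low that the choice of test hardly matters. A reader might infer from the less favourable rows that the study is too small; without an open-group rate, that is not shown.

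**Conclusion.** The point holds in two parts. First, the plan gives two required totals, 100 in two groups and 150 in three, with only the 5% loss in common and no reconciling text. This rests on the wording alone. Second, the sample-size section takes its effects from minimally invasive versus open repair but justifies the number by tests of a different null hypothesis. The 46% rejection rate with no overall minimally invasive effect shows that this is more than a matter of wording; it rests on the assumed 30%, 20% and 40% rates and equal group sizes.

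The loss of power from the three-group test is about 2 to 11 percentage points over the absolute scenarios shown, assuming equal laparoscopic and robotic rates and 1:1:1 enrolment, which a non-randomized study does not control. At 30% versus 10% it decides whether the stated 80% is met. The defect is the conflicting target and the mismatched test, not a proven shortage of patients.

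**What to change.** 1. Correct the abstract so that it gives the same total and number of groups as the sample-size section. The objective in Methods and Design already states the contrast and needs no change.
2. In the sample-size section and Statistical Analyses, name minimally invasive versus open as the primary comparison: a single 1-df contrast reported with a 95% CI and carried into the adjusted model. Make laparoscopic versus open, robotic versus open and laparoscopic versus robotic secondary.
3. Restate the power that 150 patients give for that contrast, with a stated open-group complication rate and a statement of whether the 20% reduction is absolute or relative. Give the assumed VAS SD if the pain effect is kept as a basis.

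The change is to wording and one recalculation, best made before outcomes are analysed. It has costs. The laparoscopic-versus-robotic comparison becomes explicitly secondary. The pooled estimate depends on the laparoscopic/robotic mix, which is not controlled. The restated power may also fall below 80%, in which case the plan must say so or raise the total.
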